#### Randomization

Only participants who express interest in using MyChoices for HIV prevention, meet eligibility criteria, provide informed consent, and complete a baseline assessment will be eligible for randomization (see Figure 2). Randomization will be stratified by SRV [31] and will occur in a 2:1 ratio with 40 YMSM randomized to the experimental condition (20 at each SRV) and 20 randomized to the control condition (10 at each SRV). This allocation will allow us to efficiently gather additional data on app utilization. Randomization will be based on a pregenerated list created by the iTech Analytic Core statisticians, with random blocks of size 3 or 6, and will be accessed through a Web portal.

Men who are randomized to receive MyChoices will be given brief instructions on the purpose of the app, how to access it, and an overview of how to use it. Participants will be encouraged to explore all components of the app and use it routinely.

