### Statistical Analyses

The primary analyses will summarize acceptability (mean score on the SUS) and feasibility (participants utilizing the app at least once during follow-up) of the app, overall for the intervention arm, with asymptotic normal 95% CIs. Point estimates for mean acceptability ≥50 and for proportion accessing the app >0.60 will be considered the minimum criteria for acceptability and feasibility, consistent with industry standards [28,32].

The primary efficacy analysis will compare HIV testing (defined by the proportion that self-reports at least 1 HIV test result during follow-up) between the study arms at 3- and 6-month follow-ups. Group differences in self-reported PrEP-related appointments and documented HIV test results will also be examined at each time point. Moreover, group differences in measures related to the SCT model constructs (eg, HIV testing self-efficacy) will be assessed. The distribution of all variables will be assessed, and appropriate tests will be conducted (ie, parametric chi-square test vs nonparametric Fisher’s exact test).

All analyses will use two-tailed tests of significance, with significance at alpha=.05. We will follow an intent-to-treat approach [52], analyzing participants in the study arm to which they were assigned. We will examine the equivalence of random assignment to groups with regards to key baseline characteristics, including sociodemographics, prior HIV testing patterns, and sexual risk-related variables. In the event that randomization does not work to balance these characteristics, we will assess whether baseline differences may account for differences in outcomes.

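### Baseline covariates enter the between-arm comparisons only if the arms look imbalanced, with no criterion and no statement of which result then stands; a small adjusted analysis should be fixed in advance

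*Protocol article*

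**What the plan says.** All of this is in the protocol article.

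- **Efficacy comparison** (Statistical Analyses): "The primary efficacy analysis will compare HIV testing (defined by the proportion that self-reports at least 1 HIV test result during follow-up) between the study". This is done twice, once per follow-up assessment (month 3 and month 6). The method is left as "appropriate tests will be conducted (ie, parametric chi-square test vs nonparametric Fisher’s exact test"; neither test takes account of a covariate or a stratum.
- **Error level** (Statistical Analyses): "All analyses will use two-tailed tests of significance, with significance at alpha=.05".
- **Balance check** (Statistical Analyses): "We will examine the equivalence of random assignment to groups with regards to key baseline characteristics, including sociodemographics, prior HIV testing patterns". The list is open-ended; it also names variables on sexual risk.
- **Consequence of the check** (Statistical Analyses): "In the event that randomization does not work to balance these characteristics, we will assess whether baseline differences may account for differences in outcomes".
- **Allocation** (Randomization): "will occur in a 2:1 ratio with 40 YMSM randomized to the experimental condition (20 at each SRV) and 20 randomized to the control condition". Also: "Randomization will be stratified by SRV". Prior testing and sexual risk are not stratification factors.

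No threshold for imbalance is given, and no statement of whether an adjusted result would replace the unadjusted one or sit beside it.

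**The concern.** Allocation comes from a pregenerated blocked list reached through a Web portal. A baseline difference under such a scheme is chance, so asking whether randomization worked answers no useful question. What matters is whether a covariate predicts the outcome. Prior HIV testing plausibly predicts later HIV testing, yet under this rule it is used only if it happens to look different between arms. SRV, on which randomization is stratified, plays no part in the planned test.

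Three things are at stake. Precision is lost when a strongly prognostic covariate is ignored because it looked balanced. In trials where such a covariate is imbalanced but not noticed, the unadjusted comparison is less reliable than its nominal level suggests. And because the text does not name the result that stands, the choice between adjusted and unadjusted is made after both can be seen.

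**Working it through.** **Inputs from the article:** N=60, 2:1 allocation, two-sided alpha 0.05, binary outcome (at least one self-reported test).

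**Assumed, not in the article:** balance judged at p<0.05; covariate prevalence 30-50%; the covariate-outcome strengths shown below.

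**1. Arm sizes.** 60 × 2/3 = 40 and 60 × 1/3 = 20, as stated.

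**2. Smallest continuous imbalance reaching p<0.05.** t(0.975, 58) × √(1/40 + 1/20) = 2.0017 × 0.27386 = 0.548 SD.

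**3. Smallest binary imbalance reaching p<0.05.** Take 8/20 (40%) in the control arm.
- 27/40 (67.5%) in the app arm: pooled proportion 35/60 = 0.5833; chi-square = 0.275² / (0.5833 × 0.4167 × 0.075) = 4.15, p=0.042. Flagged, at 27.5 points.
- 26/40 (65%): pooled proportion 34/60 = 0.5667; chi-square = 0.25² / (0.5667 × 0.4333 × 0.075) = 3.39, p=0.065. Not flagged, at 25 points.

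For control prevalence of 30-50%, the threshold is 27.5 points by chi-square and 27.5-32.5 points by Fisher's exact test.

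**4. How often chance imbalance goes unflagged.** Exact enumeration of two independent binomials (40 and 20), prevalence 30-50%, chi-square test:

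| Imbalance in one characteristic | Trials in which it occurs | Of these, flagged at p<0.05 |
|---|---|---|
| at least 15 points | 27-32% | 17-19% |
| at least 20 points | 14-17% | 32-38% |

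At 50% prevalence, a gap of at least 15 points occurs in 31.7% of trials and 17.3% of these are flagged, so 0.317 × (1 − 0.173) = 26% of trials carry such a gap unflagged.

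**5. Chance flags.** With k independent characteristics each tested at 0.05, P(at least one flag) = 1 − 0.95^k: 23% for k=5 and 40% for k=10.

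**6. Error and power, continuous outcome.** Simulated linear model, one covariate, 40,000 trials per setting; power at an assumed effect of 0.7 SD. This setting is more favourable to adjustment than the trial's binary endpoint.

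| Assumed correlation | 0.3 | 0.5 | 0.7 |
|---|---|---|---|
| Type I error, adjust only if p<0.05 at baseline | 4.9% | 4.3% | 3.6% |
| Type I error, always adjust | 5.2% | 4.8% | 5.0% |
| Type I error, report the better of the two | 6.5% | 7.2% | 8.2% |
| Power, adjust only if p<0.05 at baseline | 71% | 72% | 73% |
| Power, always adjust | 74% | 82% | 94% |

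**7. Error and power, binary outcome.** Simulated at 40 versus 20 with one binary covariate and an assumed odds ratio of 2 to 8.
- Overall type I error: 4.6-5.3% under the p<0.05 trigger, 4.8-5.1% with fixed stratified adjustment.
- Power: fixed adjustment ranges from 1 point worse to 7 points better than the trigger.
- Trials with an imbalance of at least 15 points that is not significant (covariate prevalence 50%, 40-50% of participants testing): the unadjusted test has type I error of about 6-8%, rising with the odds ratio.

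**The case against.** The strongest reply is that the article says less than a critic may read into it. A reader might infer three things that it does not support.

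- **That baseline differences will be tested at p<0.05.** The alpha sentence covers all analyses in general terms, and the check itself is only described as an examination. The thresholds in steps 2 to 5 therefore depend on that reading. A looser criterion would flag more, but the decision would still follow the data.
- **That an adjusted model will replace the planned test.** The sentence speaks of assessing whether differences explain outcomes. A supplementary analysis is at least as natural a reading. What stands is that the text does not settle it.
- **That the rule inflates the false-positive rate.** It does not. Over all randomizations the unadjusted test is valid, and the trigger is at or slightly below nominal. The 6-8% applies only within trials that have an unflagged imbalance. The 6.5-8.2% in step 6 needs someone to report the more favourable result, which the article does not propose but also does not rule out.

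Eligibility excludes men with a recent HIV test, which narrows the range of testing history and may weaken it as a predictor. With an odds ratio of 2 to 4 the implied correlation is only about 0.17-0.34. Logistic adjustment with 20 controls would bring sparse-data problems and would change the estimand from a difference in proportions to a conditional odds ratio. Both points stand and shape the fix.

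It can also be said that covariate lists belong in an analysis plan that is not shown. That does not dispose of the point, because the balance-triggered step is itself a stated rule.

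**Conclusion.** The point holds at modest size. Use of covariates depends on observed imbalance, without a criterion and without a named main result, and the planned test ignores the stratification factor. Overall type I error is not inflated. The cost is some precision when the covariate is strongly prognostic (up to 7 power points in the binary setting, nothing or slightly negative when it is weak), error of about 6-8% in trials with unflagged imbalance, and an open choice of what to report. These sizes rest on the assumed p<0.05 criterion and assumed odds ratios of 2 to 8.

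The reach is limited. The article says the pilot is not powered for behavioral outcomes. The usability-score and app-use criteria are summaries of the app arm alone, which imbalance between arms cannot affect. A reader might infer from Study Design, which includes preliminary efficacy in the information used for progression, that the go/no-go decision is exposed. The Abstract and Discussion tie progression to acceptability and feasibility, so that inference is weak.

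**What to change.** Replace the balance-triggered sentence with a fixed rule:

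- One HIV testing comparison at each stated time point, by assigned arm, adjusted for SRV and baseline testing history whatever the observed balance. Use a method suited to 60 participants that keeps the difference in proportions, for example a Mantel-Haenszel stratified risk difference with its confidence interval.
- Baseline characteristics by arm shown descriptively, without tests.
- The unadjusted chi-square or Fisher test, and any further adjustment, kept as labelled sensitivity analyses.

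The cost is about one paragraph. SRV is known, and Table 1 already lists HIV testing history among the data collected. There are two downsides. If testing history is weakly prognostic, a little efficiency is lost. Strata are also thin: two SRVs by a two-level testing history leave 20/4 = 5 controls per stratum on average. Adjustment should therefore stop at one or two covariates, with a rule set in advance for merging empty strata.

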## Results

Recruitment for the RCT began in October 2018, with study follow-up complete by June 2019.

## Discussion

Advances in mobile phone technologies have enabled YMSM to have immediate access to broad social and sexual networks. The proposed project responds to the increasingly widespread use of mobile technology in the United States. MyChoices is a theory-driven app that was developed by our interdisciplinary team of HIV clinicians, epidemiologists, behavioral scientists, and app developers based on feedback from a diverse sample of YMSM and will be refined and tested using scientifically rigorous research methods. Therefore, to our knowledge, MyChoices will be one of the first comprehensive, theory-driven HIV prevention apps designed specifically for YMSM. We anticipate that MyChoices will increase HIV testing and linkage to prevention services because it is developmentally appropriate and meets YMSM where they are, in an environment that is familiar and discrete.

Anticipated limitations of this protocol include the self-reported outcomes for HIV testing and PrEP uptake. We will explore obtaining more objective measures of HIV testing and PrEP uptake, including obtaining photographs of test results and PrEP prescriptions. Relatedly, by answering questions about their HIV testing history at follow-up assessments, self-reported outcomes may be influenced that could bias the results. However, the follow-up survey covers a number of topics, including mental health, stigma, and sexual behaviors, and the HIV testing questions are limited. As a result, we do not anticipate substantial misclassification. There is also a risk that participants in the intervention group may discuss with or even show the MyChoices app to participants in the standard of care group (eg, if friends or partners both enroll in the study). To reduce the risk of contamination, study staff will remind the participants at baseline not to discuss the app with peers who might be in the study.

If MyChoices demonstrates acceptability and feasibility in this pilot study, a multicity, 3-arm RCT of this app and another youth-optimized app (LYNX) versus standard of care will be conducted through iTech. If shown to be efficacious, the MyChoices app could be a scalable technology-based solution, with the ability to reach YMSM across the United States, while maintaining a “geographically individualized” feel with app content integrated with local prevention and testing activities.

## Abbreviations

CASI: computer-assisted self-interviewing
GPS: global positioning system
GIF: graphics interchange format
MSM: men who have sex with men
PrEP: pre-exposure prophylaxis
RCT: randomized controlled trial
SCT: social cognitive theory
SRV: subject recruitment venues
STI: sexually transmitted infection
SUS: System Usability Scale
YMSM: young men who have sex with men
